#### Exploratory outcome

Psychometric questionnaires used in exploratory analyses include German versions of theoAnger Rumination Scale (ARS) [35].oPersonality Disorder Scale (PDS-ICD-11) [36].oBarratt Impulsiveness Scale (BIS-15) [37].oBrief-Symptom Checklist (BSCL-53) [38].oSocial Network Questionnaire (SNQ) [39].oPersonality Inventory for DSM-5 (PID-5-BF + M) [40].oUCLA Loneliness Scale (UCLA-3) [41].oGroup Questionnaire (GQ-D) [42].oNegative Effects Questionnaire (NEQ) [43].oDifficulties in Emotion Regulation Scale (DERS-36) [44].oCertainty About Mental State Questionnaire (CAMSQ) [45].oRejection Sensitivity Questionnaire (RSQ-20) [46].Computerized behavioral tasks used in exploratory analyses (assessed online at home) includeoEmotion Classification Task [25] measuring attentional bias to threat-related stimuli by recording reaction times and error rates. Participants categorize 80 facial expressions (angry, fearful, happy, neutral) presented in a randomized order, following a fixation cross and brief stimulus display, with a response window of 3000 ms.oGrid Learning Aggression Task (GLAT; adapted from previous research on threat sensitivity) [47–49] where participants interact with several virtual agents on a grid to reach goals (similar to a PacMan game). Virtual agents can be cooperative or competitive, and the positions of the two players can be advantageous or disadvantageous for the participant. Participants rate their anger after the interaction.oEmpathy and Theory of Mind (EmpaToM) [50] paradigm assessing empathy and Theory of Mind (ToM) abilities through a computer-based task involving short videos of individuals recounting autobiographical experiences with negative or neutral emotions. Participants rate their own emotional response to measure empathy and answer content-related questions, some requiring perspective-taking, to evaluate ToM abilities.

### Participant timeline {13}

#### Sample size {14}

In our pilot study with analogous study design and analogous patient population, the effect size for the primary outcome measure (OAS-M overt-aggression score at follow-up) was 0.68 (standardized mean difference between treatment arms on a log scale). For conservative planning of sample size, we assumed an effect size of 0.55. According to a sample size design with G*Power 3.1.9 [51], a sample size of 106 (53 per group) for a *t*-test with 80% power at a significance level of 0.05 with individual randomization would be indicated. In our pilot study, the intraclass correlation coefficient (ICC) within treatment groups (unit of randomization) was 0.075, which together with an average treatment group size of 4 corresponds to a variance inflation factor of 1.225. A sample size of 130 patients is therefore required for cluster randomization. With reference to previous studies and our pilot study [52, 53], a loss-to-follow-up of patients after randomization is expected with up to 30% of the randomized participants (drop-out 186*0.3 = 56), similar in both arms. This means that 186 patients will be randomized (93 to MAAP and 93 to the NSSP intervention) in order to observe the desired number of 130 patients with sufficient data for statistical analysis until the follow-up after 24 weeks. Our pilot study also indicates that a threefold number of patients than required should be screened for inclusion in the study. Against this background, a total of approximately 550 people should be screened for study eligibility. Based on our pilot study, 36% of the patients screened (by telephone) will not be included in the randomization for various reasons (e.g., not meeting the inclusion criteria, meeting the exclusion criteria, no longer available). Consequently, about 253 patients will be included in the diagnostic screening process at T-1, leaving 186 patients available for randomization. The sample to be recruited and examined thus comprises a total of *N* = 186 patients with (subthreshold) BPD and overt reactive aggression problems.

#### Recruitment {15}

Originally, recruitment at six sites in Germany (Aachen, Bielefeld, Bonn, Frankfurt, Heidelberg, Munich) was planned that cover metropolises as well as medium-sized cities that are more or less rural in character. To ensure sufficient recruitment within the planned trial phase, a seventh study site (Berlin) has been added after trial initiation. Various recruitment strategies are implemented based on our previous experience in the pilot study. Outpatients are recruited via psychiatric and/or psychotherapeutic specialist clinics for patients with BPD by providing information about the psychotherapeutic treatment available. Patients are also recruited via referrals from outpatient psychiatrists and psychotherapists, psychiatric clinics in the community as well as via the internet (study website, social media and networks), newspapers, radio, flyers, local anti-aggression projects, and registers of previous study participants in other trials. Existing collaborations with local experts by experience and self-help groups in several locations also contribute to patient recruitment.

## Assignment of interventions: allocation

### Sequence generation {16a}

Both the experimental and control interventions are implemented as group therapy, i.e., patients are randomized in clusters of therapy groups consisting of ideally 4 to 6 participants. Cluster randomization is performed using permuted block randomization, with a 1:1 allocation ratio to the two treatment arms. As soon as a group of usually 4 to 6 eligible participants at a given site has completed all baseline assessments, randomization of the group is performed. This process is initiated by a site staff member and conducted via a dedicated online platform managed centrally by the Coordination Center for Clinical Trials (KKS) in Heidelberg. This procedure ensures that allocation is both unbiased and concealed. Randomization is stratified by study site and must be completed prior to the start of the therapeutic sessions.

### Concealment mechanism {16b}

To ensure concealment of the randomization sequence until the time of intervention allocation, the allocation process is centrally managed by the KKS (allocation service team), which acts as a central, independent entity responsible for the allocation process and follows a set of robust procedures. After successful recruitment, treatment groups, each consisting of usually 4–6 participants, are randomly assigned to one of the two treatment arms in a 1:1 ratio while allocation is implemented digitally by designated study personnel at each study site using a software program that is accessible via a website. By centralizing randomization and concealing the allocation sequence until treatment group assignment, we ensure that the process remains unbiased.

### Implementation {16c}

After the successful recruitment of groups (4–6 patients) and the scheduling of assessments and therapy, group assignment is carried out by the responsible study coordinator at each site, or another dedicated member of the study staff who is not blinded to the assigned intervention (e.g., a research assistant) during the 2-week baseline assessment period.

## Assignment of interventions: blinding

### Who will be blinded {17a}

The outcome assessors (study diagnosticians) are blinded to the assigned intervention condition. Patients and all study personnel are informed and instructed not to disclose any information about the assigned intervention groups to the diagnosticians.

### Procedure for unblinding if needed {17b}

Participants and therapists cannot be blinded due to the nature of the intervention conditions. MAAP is a structured, mechanism-based psychotherapy that uses specific therapeutic techniques which differ substantially from the non-directive, supportive approach of NSSP. As such, participants are likely to recognize the type of therapy they are receiving, rendering patient blinding infeasible. However, participants are not informed about which intervention constitutes the control condition. This minimizes expectation effects and preserves some degree of blinding regarding the purpose of treatment allocation. Therefore, a formal unblinding procedure is not applicable.

## Data collection and management

### Plans for assessment and collection of outcomes {18a}

Table 1 provides a detailed overview of the assessments and collection of outcomes. During a personal or telephone screening (phone screening, T-2), interested patients are informed about the study and receive written information. General inclusion and exclusion criteria are also roughly checked via phone screening. At the next appointment (inclusion diagnostics, T-1), after informed consent has been signed, inclusion and exclusion criteria are checked in a detailed structured clinical diagnostic interview session, and comorbid disorders are also identified. The OAS-M [27] is used to assess the frequency and severity of overtly aggressive behavior. Severe cognitive impairments (IQ < 70) are screened using the mini-q [54] as well as clinical impression.

As soon as 4 to 6 patients have been included, they are invited to the next measurement appointment (baseline, T0), during which the OAS-M and the ZAN-BPD [55] are collected again. This baseline appointment must take place in the two weeks before the start of the intervention. At the beginning of T0, patients receive an online link to several psychometric questionnaires to assess the symptoms typical of BPD, the level of personality functioning, emotion regulation, everyday functioning, quality of life, sensitivity to rejection, anger rumination and experience, loneliness, social network, experiences of trauma and neglect in childhood and adolescence, general symptom burden and mentalization skills (for detailed overview, see Table 1). Patients also complete an Emotion Classification Task [25] and a Grid Learning Aggression Task (GLAT, adapted from [47–49]) to assess threat sensitivity as well as the EmpaToM [50], a paradigm independently manipulating empathy and ToM. Furthermore, EMA is completed during these two weeks before the start of the intervention.

During the 8- to 10-week intervention phase, the therapeutic alliance and adherence to therapy are measured repeatedly using questionnaires. The intervention phase is followed by the next measurement (T1), in which the OAS-M, the ZAN-BPD, and specific psychometric questionnaires from T0 (see Table 1) are collected again, and the emotion classification and GLAT tasks are also carried out again. At the follow-up measurements T2—T4 (4, 12 and 20 weeks after the end of the intervention), the OAS-M is collected again, and the psychometric questionnaires are administered in such a way that each of the questionnaires is collected once in total over the follow-up period (see Table 1). At the last measurement time point (T5, 24 weeks after the end of the intervention), all questionnaires (except from CTQ and LHA) and all behavioral tasks are completed again, while the EMA is also completed again during the two weeks prior to T5.

**Table 1 Tab1:**
[figure not shown]
Overview of the study procedure and the assessments and collection of outcomes

IPDE (International Personality Disorder Examination for DMS-5): Suitability and assignment; MINI-DIPS for the assessment of exclusion criteria: Schizophrenia (lifetime), Bipolar I disorder (current), moderate and severe substance use disorder, and comorbidities; LHA (Life History of Aggression); mini-q: Assessment of verbal intelligence; ZAN-BPD (Zanarini Rating Scale for Borderline Personality Disorder): Measure of symptom severity; OAS-M (Overt Aggression Scale-modified): Interview-based measure of the frequency and severity of overt aggressive behavior that has occurred in a 2-week period; Items 1-3: verbal aggression, aggression against objects, aggression against others; Item 4: Aggression against oneself; Items 5–6: Irritability, subjective and visible from the outside; Suicidality: measured with item 7 and reviewed by a diagnostician with clinical expertise on an individual basis; ARS, Anger Rumination Scale; BIS-15, Barratt Impulsiveness Scale; BSCL-53, Brief-Symptom-Checklist; CAMSQ, Certainty About Mental States Questionnaire; CTQ, Childhood Trauma Questionnaire; DERS-36, Difficulties in Emotion Regulation Scale; EmpaToM, Empathy and Theory of Mind paradigm; ERC Emotion Classification task; GLAT Grid Learning Aggression Task; MEQ-16, Mentalizing Emotions Questionnaire; PDS-ICD-11, Personality Disorder Severity Scale; PD-T, Participation-related Documentation, Therapist Version; PD-P, Particpantion-related Documentation, Patient Version; PID-5-BF+M, Personality Inventory for DSM-5; RSQ-20, Rejection Sensitivity Questionnaire; SNQ, Social Network Questionnaire; SOFAS, Social and Occupational Functioning Assessment Scale; Soc.-Dem., Sociodemographic Questionnaire; STAXI-II, State-Trait-Anger-Inventory II; UCLA-3 Loneliness Assessment; WHOQoL-BREF, WHO Quality of Life; NEQ, Negative Events Questionnaire; GQ-D, Group Questionnaire, German Version

Note: Each shade corresponds to a specific phase or time point to help differentiate study phases over time. The assessment of the primary outcome is highlighted in black for easy identification

### Plans to promote participant retention and complete follow-up {18b}

In clinical studies of BPD, attrition rates of up to 30% have been reported after 6 to 12 months (e.g. [56],). Given the difficulty of follow-up in this patient population, we implement several strategies to promote participant retention and minimize missing data across all timepoints. Study personnel interacting with patients endeavor to establish and maintain communication and support through ongoing contact, which is likely to be a key factor in reducing dropout in this population. Regular contact is maintained with participants throughout the study period, including between treatment and follow-up assessments, using flexible and participant-preferred communication channels (e.g., via phone or email communication). Furthermore, follow-up assessments are scheduled with as much flexibility as possible to accommodate participants’ availability, including offering evening or remote appointments where appropriate. Participants are encouraged to complete outcome assessments even if they discontinue therapy, with dedicated research staff available to facilitate participation and resolve any barriers. Furthermore, participant reimbursement is structured to incentivize continued engagement: partial reimbursement is provided after completed assessments, with the final reimbursement amount also depending on the total number of questionnaires and EMA entries completed. This tiered approach is designed to reward ongoing participation throughout the study, aiming to reduce attrition and promote the completeness and quality of the data, particularly with regard to the primary outcome.

### Data management {19}

A dedicated data management team as part of the KKS ensures proper handling and storage of data throughout the study. This team ensures data integrity and compliance with data protection regulations. All data management processes and monitoring procedures are performed on validated systems in accordance with the current KKS SOPs and are defined in a study-specific monitoring manual (Investigator Site File, ISF). An electronic study-specific data collection form (electronic case report form, eCRF) managed by the KKS is used for data collection. The eCRF is used for data entry of all outcome measures, either directly (patient-administered psychometric questionnaires) or via paper–pencil post-collection (e.g., diagnostic interview sessions, patient and therapist documentation). All entries and corrections in the remote data collection system are automatically documented in an audit trail. The completeness, validity, and plausibility of the data are continuously checked and signed by authorized study personnel after data entry (edit checks) and with the help of validation programs that generate queries. Study participants are required to answer or clarify these queries. Once no further corrections are required, the database is closed and used for statistical analysis. At the end of the study, the data will be converted into various data formats (e.g., CSV files) to allow for reuse of the anonymized data.

### Confidentiality {27}

The names of patients and all other confidential information are subject to medical confidentiality and the provisions of the General Data Protection Regulation (GDPR) and the Federal Data Protection Act (*Bundesdatenschutzgesetz*, BDSG). Authorized representatives (persons responsible for data monitoring) who are obliged to maintain confidentiality may inspect the personal data held by the investigator insofar as this is necessary to verify the proper conduct of the study. With regard to this measure, the participants release the investigator from medical confidentiality. Other persons are not given access to original documents. Patient data may only be passed on in pseudonymized form.

### Plans for collection, laboratory evaluation and storage of biological specimens for genetic or molecular analysis in this trial/future use {33}

Not applicable, no biological specimens are collected or analyzed in this trial.

## Statistical methods

### Statistical methods for primary and secondary outcomes {20a}

Despite the cluster-randomized design, all outcomes are measured and assessed at the individual patient level. The expected superiority of MAAP over NSSP in reducing overt aggressive behavior is measured by the Overt Aggression Score (OAS-M, sum of items 1–3) at 24 weeks (primary outcome measure, T5). The superiority of the MAAP arm over the NSSP arm will be tested (at a two-sided significance level of 5%) using a linear mixed-effects model with overt aggression score as the dependent variable (using data of all post-randomization timepoints), pretreatment overt aggression score as a covariate and center, treatment arm, and time point as fixed effects, and patient ID and treatment group as random effects. The contrast between treatment arms at T5 is the parameter of interest and will be reported by effect size (standardized mean difference) and p-values as well as group-wise estimated marginal means (emmeans), all with 95% confidence intervals (CIs). Contrasts for all other post-randomization timepoints will be presented by effect size and emmeans with 95% CIs. Analyses of continuous secondary outcome measures will be performed analogously to the primary outcome measure, while analyses for binary secondary endpoints will be performed using logistic mixed-effects models.

### Interim analyses {21b}

There are no formal discontinuation criteria or stopping rules for the overall trial, as no serious health risks are expected. The intervention is considered low-risk, and similar study designs conducted by our group in the past have not resulted in any complications. In particular, a previous feasibility trial using the same interventions and procedures did not raise any safety concerns. Accordingly, no interim analyses are planned. This trial is intended to run to completion unless unexpected safety concerns arise.

### Methods for additional analyses (e.g. subgroup analyses) {20b}

Exploratory outcomes and endpoints for mediation analyses will be analyzed analogous to the primary outcome for continuous variables and using logistic mixed-effects models for binary variables. Safety data will be analyzed descriptively with lists of (S)AEs by treatment arm. To date, to the best of our knowledge, there is no evidence of gender-specific treatment effects in BPD. As men with BPD have often been neglected in BPD research [21], we plan an exploratory subgroup analysis by gender.

Data not relating to primary or secondary outcomes (e.g., baseline patient characteristics, safety data, or therapist adherence data) may be analyzed and published before the study is completed, as long as these analyses do not affect the interpretation of the primary or secondary outcomes. Such early analysis will be conducted with appropriate caution to ensure that it does not interfere with the integrity or the statistical power of the final results.

### Methods in analysis to handle protocol non-adherence and any statistical methods to handle missing data {20c}

The primary analysis will follow a modified intention-to-treat (mITT) approach, i.e., we will not include patients who do not participate in any of the randomized treatments (drop-out between eligibility and randomization, i.e., before the start of treatment). In general, the mixed-effects model uses all post-randomization measurements of the outcome of interest to test the treatment contrast at the last follow-up time point and thus effectively accounts for missing data. Only patients without any measurement except the baseline measurement do not contribute any information to this analysis. To investigate the potential impact of missing data, different sensitivity analyses are planned. Based on findings from the pilot study—where slightly more participants in the NSSP arm failed to complete T5—we do not assume that missing data are missing completely at random (MCAR), but rather potentially missing not at random (MNAR). Thus, two complementary multiple imputation strategies will be performed as sensitivity analyses. In the first multiple imputation strategy, imputation of missing outcome values at T5 will be performed separately for each treatment arm. In the second multiple imputation strategy, missing data will be imputed together for both treatment arms. A further sensitivity analysis will be carrying forward the last available overt aggression score from earlier timepoints (e.g., T4) to estimate T5 (LOCF).

Additionally, a per-protocol analysis will be performed as a further sensitivity check. This analysis will include only those participants who attended at least 9 out of 13 group sessions and did not miss more than 2 sessions in a row. This criterion is intended to ensure that only patients with adequate exposure to the assigned intervention are included in the per-protocol analysis.

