The secondary objectives, leading to eight secondary hypotheses, include further indicators of the hypothesized superiority of MAAP over NSSP. First, it is hypothesized that patients in the MAAP condition will show a significantly greater reduction in overt aggressive behavior (OAS-M) immediately after the intervention (T1) and/or at follow-up measurements 4 weeks (T2), 12 weeks (T3), and 20 weeks (T4) after the intervention compared to patients in the NSSP condition and as measured at baseline. Second, it is hypothesized that patients in the MAAP condition will show a significantly greater reduction in auto-aggressive behavior (OAS-M) and/or irritability (OAS-M) at T1 and/or at follow-up measurements T2–T5 compared to patients in the NSSP condition and as measured at baseline. Third, it is hypothesized that patients in the MAAP condition will show a significantly higher response rate (with response being defined as reduction of the OAS-M overt aggression score by at least 50% from baseline) at T1 and at all follow-up measurements (T2–T5) compared to patients in the NSSP condition. Fourth, it is hypothesized that after 24 weeks of follow-up, patients in the MAAP condition will show a significantly greater reduction in anger experience (STAXI-II) and aggressive behavior (3 additional items), as measured via EMA (8 assessments/day) over 2 weeks, than patients in the NSSP condition and as measured at baseline. Fifth, it is hypothesized that patients in the MAAP condition will show a significantly greater reduction in BPD symptom severity (ZAN-BPD) at T1, T3, and at T5 compared to patients in the NSSP condition and as measured at baseline. Sixth, it is hypothesized that patients in the MAAP condition will show a significantly greater reduction in trait anger (STAXI-II) at T1, T4, and T5 compared to patients in the NSSP condition and as measured at baseline. Seventh, it is hypothesized that patients in the MAAP condition will show a significantly greater improvement in everyday functioning (SOFAS) at T1, T2, and T5 compared to patients in the NSSP condition and as measured at baseline. Eighth, it is hypothesized that patients in the MAAP condition will show a significantly greater improvement in quality of life (WHO-QoL-Bref) at T1, T3, and T5 compared to patients in the NSSP condition and as measured at baseline.

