#### Secondary outcomes

Externally directed overt aggression in OAS-M (items 1–3) immediately after intervention and at follow-ups 4, 12, and 20 weeks after intervention.Attacks against self OAS-M (item 4), Irritability OAS-M (items 5–6) and suicidality OAS-M (item 7a/7b) at 24 weeks after intervention.OAS-M response rate (i.e., reduction in OAS-M sum of items 1–3 of at least 50% compared with baseline) at 24 weeks after intervention.Anger and aggressive behavior measured with Ecological Momentary Assessment (EMA) at 8 random time points in the 2 weeks before the 24-week follow-up (T5), adjusted for EMA at 8 random time points 2 weeks before the start of the intervention period.Symptom severity of BPD as measured by the Zanarini Rating Scale for Borderline Personality Disorder (ZAN-BPD) [31] at 24 weeks of follow-up.Anger as measured by the State-Trait Anger Expression Inventory (STAXI-II) [32] 24 weeks of follow-up.Everyday functioning as measured by the Social and Occupational Functioning Assessment Scale (SOFAS) [33] at 24 weeks of follow-up.Quality of life (WHOQoL-Bref) [34] at 24 weeks of follow-up.

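### EMA has a single post-randomization measurement period, so the claim that the mixed model deals with missing data does not hold for this secondary outcome

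*Protocol article*

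**What the plan says.** **Timing of EMA.** Plans for assessment and collection of outcomes {18a} places the first period before treatment ("Furthermore, EMA is completed during these two weeks before the start of the intervention") and the second at the end of follow-up ("while the EMA is also completed again during the two weeks prior to T5"). Its lists for T1 and for T2 to T4 do not include EMA. Under Secondary outcomes, the EMA endpoint is defined "in the 2 weeks before the 24-week follow-up (T5), adjusted for EMA at 8 random time points", that is, with the pre-treatment period as the adjustment variable.

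**Model.** Section {20a} gives the primary outcome a linear mixed model. The pre-treatment score is a covariate, all post-randomization visits are responses, and patient and therapy group are random effects. It then says: "Analyses of continuous secondary outcome measures will be performed analogously to the primary outcome measure".

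**Missing data.** Section {20c} states that "the mixed-effects model uses all post-randomization measurements of the outcome of interest to test the treatment contrast at the last follow-up time point" and takes this as the reason why missing values are handled. It adds that only patients with nothing beyond baseline drop out of the analysis. The same section rejects missingness completely at random, considers it potentially not at random, and notes that slightly more NSSP patients missed T5 in the pilot. Two multiple imputations and an LOCF of the overt aggression score are planned as sensitivity analyses.

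**Loss.** Sample size {14}: "a loss-to-follow-up of patients after randomization is expected with up to 30% of the randomized participants", assumed similar in both arms.

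**The concern.** The argument in {20c} works for the OAS-M, which is collected at T1 to T5: a patient who leaves after T2 still informs the T5 contrast through the earlier scores. It depends on repeated post-randomization values of the same outcome. EMA has one such period, so the analogous model has nothing earlier to draw on.

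EMA carries the fourth secondary hypothesis and is the only momentary, daily-life measure of anger and aggression among the secondary outcomes. Objectives {7} says the secondary results will be read for consistency across outcomes. If the EMA estimate rests on a selected subset while the OAS-M estimate uses nearly everyone, agreement or disagreement between the two is hard to interpret. A reader of {20c} would not notice the difference.

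**Working it through.** **1. The plan's own figures.** Inputs from Sample size {14}: standardized difference 0.55, power 80%, alpha 0.05 (two-sided per {20a}), ICC 0.075, group size 4, loss up to 30%.
- Two-sample t-test: 52.87, so 53 per arm and 106 in total.
- Design effect: 1 + (4 − 1) × 0.075 = 1.225; 106 × 1.225 = 129.85, so 130.
- Loss: 130 / 0.70 = 185.7, so 186; 186 × 0.30 = 55.8, so 56.

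All agree with the article.

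**2. Response values per patient.**

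| Outcome | Covariate | Responses | Lost before T5 but seen at T1 |
|---|---|---|---|
| OAS-M overt aggression | T0 | T1, T2, T3, T4, T5 | still contributes |
| EMA | pre-treatment fortnight | fortnight before T5 | contributes nothing |

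Each of the other seven secondary hypotheses in Objectives {7} names at least three post-treatment visits, so EMA is the exception. Implementation {16c} allows allocation during the baseline fortnight, so some baseline prompts may follow allocation. They remain the pre-treatment covariate and are not a second response.

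**3. Patients affected.** At 30% loss, 186 × 0.30 ≈ 56 are omitted and 186 × 0.70 ≈ 130 remain.

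**4. Power.** The article gives no EMA effect or EMA-specific loss. Borrowing 0.55 and 1.225 as assumptions, the effective number per arm is N / 2 / 1.225:

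| Assumed T5 EMA loss | N | Effective per arm | Power |
|---|---|---|---|
| 30% | 130 | 53.1 | 80.1% |
| 40% | 112 | 45.6 | 73.8% |
| 50% | 93 | 38.0 | 65.7% |

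**5. Bias (illustrative; every input is an assumption).** One large simulated trial of 200,000 patients for each setting, clustering ignored. Baseline, T4 and T5 values share a patient component with variance 0.6 of a total of 1, which gives a correlation of 0.6. The true difference is −0.55 at T4 and T5. Loss before T5 follows logit(p) = c + slope × T4 value, with c set so that 30% are lost in each arm. Complete-case: T5 regressed on arm and baseline among those observed. Imputed: missing T5 first predicted within arm from baseline and T4.

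| Slope NSSP | Slope MAAP | Complete-case | Imputed |
|---|---|---|---|
| 0 | 0 | −0.55 | −0.55 |
| 0.8 | 0.8 | −0.56 | −0.56 |
| 0.8 | 0 | −0.50 | −0.55 |
| 1.5 | 0 | −0.47 | −0.55 |
| 0 | 0.8 | −0.60 | −0.55 |
| 0 | 1.5 | −0.63 | −0.55 |

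The largest bias is 0.08 in either direction.

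A second simulation used 93 per arm and 1,500 trials per setting. It assumed a baseline-to-T5 EMA correlation of 0.5, a T4 OAS-M to T5 EMA correlation of 0.4 or 0.6, about 30% loss, and drop-out driven by OAS-M in NSSP only or in opposite directions by arm. Complete-case estimates of a true 0.55 were 0.42 to 0.50. That is a bias of 0.05 to 0.13, or 0.05/0.15 = 0.33 to 0.13/0.15 = 0.87 of the standard error of about 0.15. With equal slopes the bias was 0.015 or less.

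**The case against.** **The missing-data section is about the primary analysis.** It opens with the primary analysis, and its LOCF names the overt aggression score. But the disputed sentence is worded generally, for whatever outcome is of interest, and {20a} sends continuous secondary outcomes to the same model. It is true that {20c} discloses that baseline-only patients drop out. It does not say that for EMA this means everyone without T5 EMA.

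**This is detail for the analysis plan.** The choice of imputation predictors is, and their absence is no fault here. The point is narrower: the article states a rule and a justification, and the justification fails for a named outcome.

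**Multiple imputation is already planned.** It is not expressly limited to the OAS-M, and the by-arm version could be read to cover EMA. It is a sensitivity analysis, however, so the main EMA estimate stays complete-case.

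**EMA is intensive.** Objectives {7} describes it "as measured via EMA (8 assessments/day) over 2 weeks", so up to 8 × 14 = 112 prompts per period. That helps with single missed prompts, not with a patient who has no T5 EMA at all.

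**The bias is built from assumptions.** This stands. Loss is planned as similar in both arms, and the pilot difference was slight. In the simulations T4 aggression drives loss and is also the imputation predictor, so recovery of the true value is built in. Patients lost before T4 would have less to impute from.

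**Further inferences that the documents do not support.** A reader might infer that LOCF breaks down for EMA, but it is planned only for the overt aggression score. A reader might also infer that the patient random effect cannot be estimated. That follows only if EMA is reduced to one score per patient, which is not stated; with momentary records it is estimable and needed.

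**Conclusion.** The point holds for one secondary outcome. As written, the main EMA analysis is a baseline-adjusted complete-case comparison at T5, and the general assurance in {20c} does not apply to it. Up to about 56 of 186 patients would be omitted if T5 EMA loss equals the 30% maximum planned for overall loss.

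Two stronger readings should be resisted. The first is that the EMA comparison is underpowered: at the planned loss about 130 patients remain, the number the trial was sized for, and power falls lower only if EMA loss exceeds 30%, about which the article says nothing. The second is that the EMA effect will be understated: the direction depends on which arm loses its more aggressive patients, and the simulated sizes are illustrations, not forecasts. If drop-out relates to aggression in the same way in both arms, the bias is negligible.

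What remains is possible selection bias of unknown sign, in a trial that itself suspects informative missingness, when OAS-M data already being collected could reduce it. The primary analysis is unaffected. The change should be made before the data are analysed.

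**What to change.** - In {20c}, limit the statement that the mixed model handles missing data to outcomes with two or more post-randomization visits.
- In {20a}, take EMA out of the analogous rule. Make its main analysis a comparison of the arms at T5, adjusted for baseline EMA and centre, with therapy group as a random effect, and a patient random effect if momentary records are modelled.
- In that main analysis, multiply impute missing T5 EMA within arm, using baseline EMA and all available OAS-M overt aggression scores from T0 to T5.
- Report the complete-case EMA result as a sensitivity analysis.

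The cost is a wording change and one imputation model on data already collected, with no new patients or visits. The drawback is some extra analysis work and reliance on missingness at random given the OAS-M scores. That reduces the concern about missingness not at random but does not remove it. Trial status plans the last patient out for November 2026, so the change can be fixed before the follow-up data are complete.
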